## Abstract

**Background:**

The impact of digital device use on health and well-being is a pressing question. However, the scientific literature on this topic, to date, is marred by small and unrepresentative samples, poor measurement of core constructs, and a limited ability to address the psychological and behavioral mechanisms that may underlie the relationships between device use and well-being. Recent authoritative reviews have made urgent calls for future research projects to address these limitations. The critical role of research is to identify which patterns of use are associated with benefits versus risks and who is more vulnerable to harmful versus beneficial outcomes, so that we can pursue evidence-based product design, education, and regulation aimed at maximizing benefits and minimizing the risks of smartphones and other digital devices.

**Objective:**

The objective of this study is to provide normative data on objective patterns of smartphone use. We aim to (1) identify how patterns of smartphone use impact well-being and identify groups of individuals who show similar patterns of covariation between smartphone use and well-being measures across time; (2) examine sociodemographic and personality or mental health predictors and which patterns of smartphone use and well-being are associated with pre-post changes in mental health and functioning; (3) discover which nondevice behavior patterns mediate the association between device use and well-being; (4) identify and explore recruitment strategies to increase and improve the representation of traditionally underrepresented populations; and (5) provide a real-world baseline of observed stress, mood, insomnia, physical activity, and sleep across a representative population.

**Methods:**

This is a prospective, nonrandomized study to investigate the patterns and relationships among digital device use, sensor-based measures (including both behavioral and physiological signals), and self-reported measures of mental health and well-being. The study duration is 4 weeks per participant and includes passive sensing based on smartphone sensors, and optionally a wearable (Fitbit), for the complete study period. The smartphone device will provide activity, location, phone unlocks and app usage, and battery status information.

**Results:**

At the time of submission, the study infrastructure and app have been designed and built, the institutional review board of the University of Oregon has approved the study protocol, and data collection is underway. Data from 4182 enrolled and consented participants have been collected as of March 27, 2023. We have made many efforts to sample a study population that matches the general population, and the demographic breakdown we have been able to achieve, to date, is not a perfect match.

**Conclusions:**

The impact of digital devices on mental health and well-being raises important questions. The Digital Well-Being Study is designed to help answer questions about the association between patterns of smartphone use and well-being.

**International Registered Report Identifier (IRRID):**

DERR1-10.2196/49189

## Introduction

The impact of digital device use on health and well-being is a pressing question to which individuals, families, schools, policy makers, legislators, and digital designers are all demanding answers [1]. However, the scientific literature on this topic to date is marred by small and unrepresentative samples, poor measurement of core constructs (eg, device use and smartphone addiction), and a limited ability to address the psychological and behavioral mechanisms that may underlie the relationships between device use and well-being [2-5]. A number of authoritative reviews have made urgent calls for future research projects to address these limitations [6-9]. The critical role of the research is to identify which patterns of use are associated with benefits versus risks and who is more vulnerable to harmful versus beneficial outcomes, so that we can pursue evidence-based product design, education, and regulation aimed at maximizing benefits and minimizing the risks of smartphones and other digital devices.

Leveraging objective data from smartphones and wearables is needed to advance scientific research in this area. Physiological and behavioral biomarkers that can be measured by smartphones and wearables present a valuable way of identifying those at risk and measuring risk factors. Promising prior research has found that longitudinal smartphone and wearable data can be used to predict and, perhaps more importantly, complement existing clinical measures [7,10,11]. Indeed, the variables that can be captured by these devices can help us understand some of the most important determinants of health. For example, behavioral risk factors such as poor mental health, sleep, and physical activity are the greatest predictor of preventable illness and death [12], and nearly 8% of the US gross domestic product is lost to mental disorders each year [13]. However, mental and behavioral health conditions are complex and multifaceted phenomena, and measurement is nontrivial. Illness can manifest in a wide range of symptoms [14] that impact both physiological states and behavior. While there are examples of impressive longitudinal studies [7,15], the scientific literature on these topics is still dominated by studies with small and often unrepresentative samples, poor measurement of core constructs (eg, device use), self-reported measures of behavior that may not correlate with objectively measured end points, and a limited ability to address the psychological and behavioral mechanisms that may underlie the relationships between device use and well-being. For example, some studies focus solely on college students [15] or medical interns [7]. A number of recent authoritative reviews have made urgent calls for future research projects to address these limitations [7-9,16].

To address this gap in the literature, we have designed a large-scale intensive longitudinal study (the Digital Well-Being [DWB] study) to analyze the relationships among smartphone use, physiological and behavioral data from wearables and smartphones, and self-reported measures of mental health and well-being. We will recruit up to 14,000 participants who opt-in to complete intake and outtake surveys and daily ecological assessments and enable sensing of features from their smartphone. In addition, at least 50% (n=7000) of the participants will wear a smartwatch (Fitbit). Each individual’s participation in the study will be for 28 days.

The aims of the DWB study are manifold. We aim to (1) provide normative data on objective patterns of smartphone use and describe how these patterns of use vary with age, gender, geography, and functioning or mental health; (2) identify how patterns of smartphone use impact well-being and who is most vulnerable to harmful effects related to smartphone use; (3) identify groups of individuals who show similar patterns of covariation between smartphone use and well-being measures across time; (4) examine sociodemographic and personality or mental health predictors; (5) examine which patterns of smartphone use and well-being are associated with pre-post changes in mental health and functioning and compare the predictive capacity of these objective measures to relevant self-report measures (eg, smartphone addiction measures); (6) discover which nondevice behavior patterns (eg, sleep, physical activity, geographic movement, and social interactions) mediate the association between device use and well-being; (7) identify and explore recruitment strategies to increase and improve the representation of traditionally underrepresented populations; and (8) provide a real-world baseline of observed stress, mood, insomnia, physical activity, and sleep across a representative population.

Next, the methods used in our data collection protocol and preliminary statistics on the demographic profile of the first cohort of participants will be described.

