## Methods

### Study Design

The DWB study is a prospective, nonrandomized study to investigate the patterns and relationships between digital device use patterns, including sensor data from phones and wearables reflecting both behavioral and physiological processes and self-reported measures of mental health and well-being. The study is 4 weeks long with passive sensing from a smartphone, and optionally a wearable (Fitbit), for the complete study period (Figure 1).

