#### Wave 2 (Augmented Enrollment)

Upon the completion of wave 1, wave-2 efforts will discontinue the enrollment of sufficiently represented groups and focus entirely on increasing the participation of underrepresented groups, as defined by race and ethnicity (eg, African American, Asian, Latina or Latino, Native Americans or Indigenous, and White populations), biological sex at birth (female and male), age (18-40 and over 40 years), sexual orientation or gender identity (heterosexual and lesbian, gay, bisexual, transgender, queer, intersex, and asexual), and whether participants are Fitbit users. Multistakeholder engagement refers to the study’s collaboration with major stakeholders such as active groups or key opinion leaders of underrepresented groups of interest to codevelop adaptive recruitment goals and strategies.

The study will aim to recruit a study sample that reflects enriched participation of traditionally underrepresented groups in the United States. The wave-2 targeted recruitment strategy will include 5 demographic factors in addition to the ownership of Fitbit devices. If wave-1 enrollment is not sufficiently at parity with population representation, wave-2 efforts will target up to an additional 4000 participants to demographically balance the aggregate sample (potential total n≤14,000).

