#### Wearable Data

We will collect the following data from participants who sign up with Fitbit devices. As access to devices can vary, participation is allowed with any generation of Fitbit devices. Different Fitbit devices have different sensors and algorithmic capabilities, and therefore not all the measures described below will be available for all participants. Minute-level features include accelerometer-based measures of steps and photoplethysmography-based heart rate measurements. Day-level features include accelerometer-based measures of activity (eg, total steps, number of floors climbed, and number of active zone minutes), sleep stages, duration and quality, minutely heart rate, daily resting heart rate, respiration rate during sleep, heart rate variability during sleep, skin temperature during sleep, blood oxygen saturation during sleep, and tonic electrodermal activity.

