## Discussion

### Principal Findings

There is a pressing need for more research into the role that digital device use plays in mental health and well-being and how these devices may be used to better monitor symptoms and complement existing clinical measures. The DWB study is an intensive longitudinal study designed to collect representative data across a large and representative population in the United States to help answer questions about the interaction between digital device use and mental health. At the time of writing, data collection is underway, with over 4000 participants enrolled.

A study of the general population means we cannot draw the same conclusions as a study of a more specific, narrow group. Unlike studies of medical interns or undergraduate students [15,38,39], where there may be some common stressors (eg, start of an internship or an examination period) that might impact all participants within a similar time frame, this study represents a much more diverse population.

Although we have made many efforts to sample a study population that matches the general population, the demographic breakdown we are able to achieve will likely not be a perfect match. This is evidenced by our study sample to date and is in part due to the desire to recruit participants with Fitbit wearable devices, a customer population that does not match the general population. It is not possible to provide participants with these devices, we therefore rely on people enrolling who have access to a Fitbit; as a result, it may be difficult to reach enough people from every demographic. Nevertheless, our initial study sample shows a promising picture that we will come close to achieving the goals.

Given the scale and nature of the study, we had to balance privacy and adherence considerations with the desire to collect highly descriptive digital data. The choice of digital probes is a product of this process. We wanted to understand sleep, mobility, physical activity, and social connectedness and, therefore, selected the digital signals informed by the desire to understand these behavioral processes. We recognize that more detailed logging (eg, app-level names) would be helpful, but these would also contain significantly more privacy sensitive data.

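### Aim 8 promises observed sleep for a representative population, but the only device-measured sleep listed comes from Fitbit owners, and balance is sought for the whole sample, not within that subset

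*Protocol article*

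**What the plan says.** The Introduction lists as aim 8 to "provide a real-world baseline of observed stress, mood, insomnia, physical activity, and sleep across a representative population". The same section sets the size of the study, "We will recruit up to 14,000 participants who opt-in", and the wearable share, "at least 50% (n=7000) of the participants will wear a smartwatch (Fitbit".

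Study Design describes "passive sensing from a smartphone, and optionally a wearable (Fitbit", so the wearable is not a condition of entry. Under Wearable Data the article says "We will collect the following data from participants who sign up with Fitbit devices", and the list that follows contains "sleep stages, duration and quality". It adds that device generations differ and that some measures will be missing for some users. The Mobile Data section lists screen and app use, mobility, activity recognition and battery status; sleep is not on it.

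Survey Instruments gives the PROMIS sleep disturbance and sleep-related impairment forms to all participants.

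The Wave 2 section names five demographic factors plus Fitbit ownership as targeting factors. Its purpose is "to demographically balance the aggregate sample (potential total n≤14,000". Table 1 compares the whole sample with the census and is not split by Fitbit status.

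Principal Findings says that devices cannot be supplied, so "we therefore rely on people enrolling who have access to a Fitbit", and that Fitbit customers differ demographically from the country as a whole. It offers this as a reason why the overall sample may miss its targets, not as a limit on the sleep baseline.

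**The concern.** A baseline for a population needs either a measure taken on a sample that resembles that population, or an adjustment that makes it do so. Here the enrolled sample and the sample with device-measured sleep are different groups. The second is selected by ownership of a consumer product, and the article itself says these owners are not typical.

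Meeting the recruitment benchmark would not reveal the problem. Owners and non-owners can depart from the census in opposite directions and cancel in the total, so the aggregate looks balanced while the group that supplies the sensed-sleep values does not. With several thousand users the interval around a mean would be narrow, and a reader could take that precision for accuracy about the US adult population.

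**Working it through.** **1. The plan's own figure.** 0.50 × 14,000 = 7000, which agrees with the Introduction. As this is a floor on Fitbit users, the number without a Fitbit is at most 14,000 − 7000 = 7000, or 50%.

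**2. Sensed sleep may be missing for more than that.** Let c be the share of Fitbit users whose device yields usable sleep output. The article gives no value, so c is an assumption. At the 50% floor, the share of all participants without sensed sleep is 1 − 0.5c:

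| c | n with sensed sleep | share without |
|---|---|---|
| 1.0 | 7000 | 50% |
| 0.9 | 6300 | 55% |
| 0.8 | 5600 | 60% |
| 0.7 | 4900 | 65% |

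**3. Aggregate balance does not fix the subset.** The census figures are those in Table 1.

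- Black, 14%: 0.14 × 14,000 = 1960. Among 7000 Fitbit users the share could be anything from 0% to 1960/7000 = 28%.
- Hispanic or Latino, 20%: 0.20 × 14,000 = 2800, so 0% to 2800/7000 = 40%.
- A less extreme split: 7% of 7000 Fitbit users (490) and 21% of 7000 others (1470) add to 1960, exactly 14% overall.
- An illustration by wave: assume that wave 1 is 10,000 Fitbit users with the 6% Black share seen so far (600), and wave 2 is 4000 non-users. Then 1960 − 600 = 1360 Black recruits in wave 2 bring the aggregate to 14%, while the sensed-sleep group stays at 6%.

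These are bounds and examples, not forecasts. They show that the stated goal can be met in full without constraining the subset.

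**4. What this could do to a mean.** Let f be the share with sensed sleep and d the owner minus non-owner difference in mean sleep. The owner mean minus the full-sample mean is (1 − f) × d. Neither d nor the standard deviation is in the article. Assume f = 0.5, an SD of 60 minutes, and d of 5, 10 or 15 minutes:

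- standard error = 60/√7000 = 0.72 min (95% half-width 1.96 × 0.717 = 1.4 min);
- bias = 2.5, 5.0 or 7.5 min, which is 3.5, 7.0 or 10.5 standard errors.

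If d is zero there is no bias. The form of the result is general; the minutes are only illustrative.

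**The case against.** The strongest reply is that aim 8 says observed, not sensed. Its list includes stress and mood, which this study measures by self-report, so the word cannot mean device-measured only. PROMIS sleep is collected from everyone. This stands. A reader might infer that aim 8 cannot be met for sleep at all; the article does not support that. The problem is confined to device-measured sleep.

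Other stronger readings also fail:

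- *Recruitment ignores the Fitbit.* It does not: ownership is a wave 2 targeting factor, and targets are revised after wave 1. What is not stated is demographic balance within Fitbit users. Recruiting towards a number of owners does not supply it.
- *Sleep cannot be measured without a Fitbit.* The phone list has no sleep measure, but screen, activity and charging signals are collected, and the Analysis Plan names bed and rise times and sleep duration without naming a device. Phone-derived sleep is unlisted, not ruled out.
- *The sleep mediation result is presented as representative.* The article makes no such claim for mediation, and the bias formula above concerns a mean, not a mediation path.
- *The baseline is known to be wrong by several minutes.* The difference and the SD are assumed.

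It can also be said that Fitbit selection is disclosed, and that weighting belongs in a fuller analysis plan. The disclosure is real, but it is not applied to the sleep baseline. The lack of a weighting method in an article is not the fault raised here. The fault lies in the scope of a stated aim and in the sample to which the balance goal applies, and both are stated in this document.

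**Conclusion.** The point holds for device-measured sleep. As described, it comes from self-selected owners of one product. At the stated floor up to 7000 of 14,000 participants have no listed value, and the number is larger if some models lack the measure. Reaching the aggregate balance goal would not make this subset representative.

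The conclusion rests on two readings: that the Mobile Data list is complete as regards sleep, and that no balance target within Fitbit users exists beyond what the article states. If phone-derived sleep is planned, the gap shrinks, but the source then has to be named, because phone and Fitbit sleep would be different measurements. The size of any bias in minutes is unknown from the document. PROMIS sleep is not affected by Fitbit ownership.

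**What to change.** 1. Restate aim 8 by data source: the whole-sample sleep baseline is PROMIS sleep, and the device-measured baseline is for Fitbit users.
2. In the Analysis Plan, name the device that supplies the sleep features used in the mediation example.
3. Tabulate demographics and baseline PROMIS sleep by Fitbit status, beside the census figures (for demographics) and the full-sample figures.
4. Standardise the device-measured sleep norms to the full enrolled sample on those variables, and label the unstandardised figures as Fitbit users only.

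All the variables are already collected. The cost is a narrower claim, one table, one weighting step and slightly wider intervals. For example, reweighting a subset from 7% to 14% Black on that variable alone multiplies the variance by about 0.14²/0.07 + 0.86²/0.93 = 1.08, so a standard error of 0.72 becomes about 0.74. Standardisation removes only the differences explained by the chosen variables. It also brings the norms to the enrolled sample, which may itself still differ from the census; hence the table in step 3.

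Forcing demographic balance within Fitbit users through recruitment is a separate choice. It would compete for at most 4000 wave 2 places, and devices cannot be supplied. It is a trade-off for the sponsor and is not needed for the changes above.

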## Methods

### Study Design

The DWB study is a prospective, nonrandomized study to investigate the patterns and relationships between digital device use patterns, including sensor data from phones and wearables reflecting both behavioral and physiological processes and self-reported measures of mental health and well-being. The study is 4 weeks long with passive sensing from a smartphone, and optionally a wearable (Fitbit), for the complete study period (Figure 1).

**Figure 1 figure1:**

The design of the 4-week intensive digital sensing study. Participants will complete baseline and poststudy assessments, and the first and last weeks of the study involves daily intensive ecological momentary assessments. Mobile sensing consisting of measurements from a smartphone, and optionally a wrist-worn wearable, will be conducted throughout the study. EMA: ecological momentary assessment.

### Recruitment

#### Overview

A key goal of the study is to explore methods to collect a representative study sample that reflects the relative proportions of various demographic subgroups and their intersectionalities in adults of the US population. For example, according to the US Census Bureau [17], 51% of the population is female and 44% of adults are between 20 and 44 years of age. Among those who reported a single race, about 13% are African American, 6% are Asian, and 74% are White. A February 2021 Gallup poll [18] reported that 5.6% of US adults identified themselves as lesbian, gay, bisexual, or transgender; 86.7% said that they were heterosexual or straight; and 7.6% refused to answer. In the past, some subgroups have been traditionally underrepresented in health studies (eg, female individuals; African American individuals; and those with a lesbian, gay, bisexual, transgender, queer, intersex, and asexual orientation) [19], and recent reviews have emphasized the importance of setting explicit recruitment goals in overcoming these biases [19,20]. As such, a key aim of the study is to learn more about how to increase the participation of traditionally underrepresented groups in digital health studies.

To explore methods to overcome recruitment barriers of traditionally underrepresented subgroups and make sure the study sample reflects sufficient diversity, we will pursue a two-prong approach: (1) a primary-augmented 2-wave metered recruitment schema and (2) multistakeholder engagement. Metered recruitment schema refers to the potential delay of eligible study participants in consent and enrollment (baseline characterization and initiation into the monitoring portion of the study). The pace of enrollment will be adapted based on study and clinical bandwidths and the distributions of demographic characteristics, with metering instituted by invitation to consent. The research team plans to begin the metered recruitment strategy once the study has achieved or has nearly achieved the enrollment of 10,000 participants. Depending on the distribution of key demographic variables, once consent and appropriate permissions are obtained, enrollment and initiation of monitoring will commence. To help reduce the effect of seasonality and other external factors on the data collected in this study, we are careful to design the strategy to recruit participants in a balanced manner across time and outside of periods containing major seasonal holidays.

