## Results

At the time of submission, the study infrastructure and app have been designed and built, the institutional review board of the University of Oregon has approved the study protocol, and data collection is underway. Data from 4182 enrolled participants have been collected as of March 27, 2023.

Table 1 shows the distribution of participants enrolled in the DWB study at the time of writing. We have been able to achieve a demographic split relatively similar to the 2021 US Census data [17] in terms of race, biological sex, age, and sexual orientation.

Figure 3 shows the geographic distribution of the participants based on home state. This map illustrated the geographic representation enabled by performing a study with our mobile platform and ubiquitous wearable and smartphone sensing.

**Table 1 table1:** Comparison between our study sample and the demographic breakdown of the US adult population. Statistics as of March 27, 2023.

Factor (level)		2021 US census [17], %		Digital Well-Being study, %

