**Orientation**				
	Heterosexual	88	78	
	LGBTQIA+^b^	8	20	
	I prefer something else	2	2	
	I do not know	2	N/A	

^a^N/A: not available.

^b^LGBTQIA: lesbian, gay, bisexual, transgender, queer, intersex, and asexual.

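### The Recruitment Overview and Table 1 give age benchmarks that cannot plausibly both be right, so the claimed age match is unverified and wave-2 parity has no settled reference

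*Protocol article*

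**What the plan says.** Methods, Recruitment, Overview gives population figures as examples of what a representative sample should reflect. Citing the census (reference 17), it says that "51% of the population is female and 44% of adults are between 20 and 44 years of age".

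The Results give a second set of figures in Table 1, titled "Comparison between our study sample and the demographic breakdown of the US adult population". Its benchmark column cites the same reference 17. It shows 55% aged 18-40 and 45% aged 40+, against 54% and 46% in the study. For biological sex it shows 48% male and 48% female, against 32% and 65% in the study. The text introducing the table names age and sex among the factors on which the sample is relatively similar to the census.

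Under Wave 2 (Augmented Enrollment), age (18-40 and over 40) and sex are among the listed factors, and "wave-2 efforts will discontinue the enrollment of sufficiently represented groups and focus entirely on increasing the participation of underrepresented groups". Up to 4,000 further participants are to be sought if wave 1 falls short of parity with the population. The section does not say which population figures define parity.

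**The concern.** The two age figures share a reference and an adult base, and their age ranges largely overlap. Yet the range that stops at 40 carries the larger share. It adds only ages 18 and 19 and drops ages 41 to 44, so it should not be 11 points higher.

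Representativeness is a stated key goal of the study, and wave 2 stops enrolling groups judged adequately represented. Against 55%, a sample with 54% aged 18-40 looks on target and leans slightly towards more younger recruits. Against a benchmark in the forties, the same sample has too many younger adults, and the over-40 group is the one to recruit. The choice of benchmark can therefore reverse which age group wave 2 pursues.

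**Working it through.** **Inputs.** From the Overview: 44% of adults aged 20-44; 51% female. From Table 1: benchmark 55% aged 18-40, sample 54%; benchmark 48% male and 48% female. From the Results: n = 4,182. From the wave descriptions: 10,000 participants in wave 1 and up to 4,000 in wave 2.

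**1. Can both age figures hold?** Ages 18-40 consist of 18-19 plus 20-40, and 20-40 lies inside 20-44. Hence share(18-40) ≤ 44% + share(18-19).
- For 55%, share(18-19) must be at least 55 − 44 = 11%, even with nobody aged 41-44. With the most favourable rounding it is 54.5 − 44.5 = 10.0%.
- Per year of age, that is 11/2 = 5.5%, against 44/25 = 1.76% on average for ages 20-44: a ratio of 3.1. With the favourable rounding it is 5.0/1.78 = 2.8.
- If ages 20-44 are spread evenly, so that some adults are aged 41-44, ages 18-19 would need 55 − 21 × 1.76 = 18.0%.
- If adults in the Overview means ages 20 and over, ages 18-19 would need 0.11/0.56 = 19.6%.

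None of these is credible.

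**2. If the 44% is right.**
- Even spread: 23 years × 1.76% = 40.5% aged 18-40. The sample is 54 − 40.5 = 13.5 points above it.
- Ceiling, assuming ages 18-19 are 3-5% of adults and nobody is aged 41-44: 47-49%. The sample is 5-7 points above it.
- Sampling error does not explain this: SE = √(0.54 × 0.46/4,182) = 0.8 points, 95% CI 52.5% to 55.5%.

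**3. If the 44% is really a share of the total population.** Assume adults are 75-80% of the population. Ages 20-44 are then 44/0.80 = 55% to 44/0.75 = 59% of adults. On an even spread, ages 18-40 are 23/25 of that, about 51-54%, which is close to Table 1.

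**4. Effect on wave 2 (illustration).** Assume 10,000 enrolled with 54% aged 18-40 (5,400), and all 4,000 further places filled. Younger recruits needed = benchmark × 14,000 − 5,400.

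| Benchmark for 18-40 | Younger recruits needed of 4,000 |
|---|---|
| 55% | 7,700 − 5,400 = 2,300 |
| 49% | 6,860 − 5,400 = 1,460 |
| 47% | 6,580 − 5,400 = 1,180 |
| 40.5% | 5,670 − 5,400 = 270 |

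**5. Other Table 1 benchmark columns.** Sex: 48 + 48 = 96%, with no benchmark entered for the third category; rescaled, 48/96 = 50% female. Race: 7 + 14 + 1 + 76 + 5 = 103%. Ethnicity, age and orientation each sum to 100%.

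**The case against.** The strongest reply is that nothing shows Table 1 to be the wrong source. A reader might infer that 55% is impossible and the age match false. Both follow only if the 44% is correct, and a denominator slip in the Overview would leave 55% roughly plausible. Even the incompatibility is not pure arithmetic: it needs ages 18-19 to be under 10-11% of adults, which is a safe assumption but comes from outside the document. This reply stands as far as it goes. It changes the conclusion from false to unverified, but one of the two places still needs correcting.

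Second, the article never says that either set of figures governs wave 2. The Overview offers its figures as examples, Table 1 is an interim comparison, and wave-2 targets are to be revised after wave 1. So it cannot be said that recruitment will be steered the wrong way. Parity still needs a reference, and the only two offered for age conflict.

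Third, a reader might take the gap between 2,300 and 270 as about 2,000 misallocated places. That uses the even-spread benchmark alone, treats age in isolation, and assumes that the interim 54% persists and that every wave-2 place is filled. At the 47-49% ceiling the gap is 840 to 1,120. Merely raising 54% to 55% from 10,000 would take about 100/0.45 = 222 younger recruits. Nor does the article plan any age weighting that could be distorted.

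Fourth, not every difference between text and table is a contradiction. The race figures in the text are restricted: "Among those who reported a single race, about 13% are African American, 6% are Asian, and 74% are White". Overlapping race categories could explain the table's 103%. The text's figure that "5.6% of US adults identified themselves as lesbian, gay, bisexual, or transgender" comes from a Gallup poll and uses different categories from the table. These call for a source note only. The 51% female figure is for the population and the 48% for adults, which may explain part of that difference but not a column total of 96%. The sample's 65% female is above either figure, so the direction of any sex targeting is unchanged.

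Finally, the article already concedes that its sample is not a perfect demographic match. That does not disclose a conflict in the benchmark itself.

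**Conclusion.** The concern holds in limited form. The age benchmarks in the Overview and Table 1 cannot plausibly both be right, and the stated similarity on age is unverified until the source is checked. If the 44% is correct as worded, the sample over-represents adults aged 18-40 by about 5-14 points. The lower end assumes that ages 18-19 are 3-5% of adults and nobody is aged 41-44; the upper end assumes an even spread within ages 20-44. If the 44% is a share of the total population, with adults assumed to be 75-80% of it, Table 1 is roughly right and the match may stand. The document does not show which figure is in error.

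The sex benchmark is also inconsistent and incomplete, with less consequence. The age conflict is more than clerical, because it bears on a claimed result and could reverse which age group wave 2 closes.

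**What to change.** Before wave-2 targets are set:

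1. Recompute the 18-40, over-40 and sex shares from one dated source on one adult (18+) base, and correct whichever of the Overview and Table 1 is wrong.
2. Label the age bands consistently as 18-40 and over 40. Table 1's 40+ overlaps with 18-40 at age 40; the wave-2 text does not.
3. Note under Table 1 the source of the orientation benchmarks, which now sit under a census heading, and why the race benchmarks total 103%.
4. Name the benchmark that governs wave-2 parity.
5. Reassess the statement that the sample is similar on age, and which age group counts as sufficiently represented.

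The cost is about an hour of table work, plus revised recruitment targets if the age benchmark moves. With 4,182 enrolled at the time of writing, and metered recruitment planned only near 10,000, there was time to do this. The possible price is a less favourable age comparison.
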